#### Inclusion criteria for randomisation

Delirium, as assessed with the Intensive Care Delirium Screening Checklist (ICDSC ≥4) or the Confusion Assessment Method for the ICU (positive CAM-ICU assessment), at the time of ICU admission or any ICU day after ICU admission.Written informed consent obtained from the patient or their legal representative.All eligibility *in*clusion criteria (from above) are still met.

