### Statistical analysis

### Primary and secondary study parameter(s)

Statistical analysis will be done according to intention-to-treat principle. All randomised participants will be included. The primary outcome is DCFDs, defined as the number of days in the first 14 days after randomisation during which the patient is alive without delirium and not in coma from any cause.^7^ Patients who are discharged before the 14-day study period has ended will be recorded as delirium and coma free after discharge.^8 35^ In addition, we will assume all patients who died within 14 days after randomisation to have 0 DCFDs.^7^ Differences between DCFDs between the haloperidol group and placebo group will be analysed using Poisson regression analysis, with adjustment for differences in baseline characteristics between treatment groups (when present) and for the different centres. We will collect data with regards to baseline demographics: age, sex, admission diagnosis category, APACHE II and APACHE IV, Sequential Organ Failure Assessment (SOFA) score, ICU days before study entry and pre-admission delirium duration in participants with delirium on admission. Pre-defined sub-analyses will include efficacy stratified by (1) agitated, mixed-type or hypoactive delirium; (2) the presence of hallucinations or delusions; (3) delirium severity (based on ICDSC score: low delirium severity=mean ICDSC score of 4 to 5; medium delirium severity=mean ICDSC score 5 to 7; high delirium severity=ICDSC score 7 to 8); and (4) sedation-related, hypoxic, metabolic or septic delirium. For cognitive and functional outcomes assessed with designated test batteries, non-parametric or parametric tests will be used depending on normality of scaled test results. Mortality risk will be assessed as a binary endpoint. A more detailed statistical analysis plan, to be drawn up before Data Base Lock, will be drafted for publication separately.

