### Sample size calculation

To achieve statistically significant results (p<0.05) with a power of 90% and a true treatment difference of 1 day for the primary outcome (from 3.2 DCFDs in the placebo group to 4.2 in the haloperidol group, SD in both groups is equal to 4.2), 371 patients are needed in each group (n=742). These estimates are derived from the previous implementation study, which included 4727 patients in three 4-month periods in the same six participating ICUs and found delirium incidence of 27% (and increase of DCFDs from 60% to 70%).^33^ Consequently, presuming an informed consent rate of 40%, we need 18 months to encounter 1900 patients with a newly diagnosed delirium to include the required 742 patients. Because of estimated workload due to follow-up visits, including, for example, neurocognitive testing, we propose to select a convenience sample of two-thirds of ICU survivors (estimated around 400 of 575 survivors) as a random sample for the cognitive, functional and secondary outcome variables.

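### The ICDSC severity strata share the scores 5 and 7, use a mean with no stated window in only two of three strata, and cannot place patients assessed by CAM-ICU alone

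*Protocol article*

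**What the plan says.** In the protocol article, the section on primary and secondary study parameters lists four pre-defined sub-analyses of efficacy. The third is by delirium severity, based on the ICDSC: "low delirium severity=mean ICDSC score of 4 to 5; medium delirium severity=mean ICDSC score 5 to 7", and then "high delirium severity=ICDSC score 7 to 8". The first is "efficacy stratified by (1) agitated, mixed-type or hypoactive delirium", with no rule or time window for the subtype. The same section says that a more detailed statistical analysis plan will be written before database lock.

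Under the inclusion criteria for randomisation, either instrument is enough: "Delirium, as assessed with the Intensive Care Delirium Screening Checklist (ICDSC ≥4) or the Confusion Assessment Method for the ICU (positive CAM-ICU assessment". Table 1 lists CAM-ICU/ICDSC and RASS three times daily during the ICU study period.

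**The concern.** The bands are printed as a rule fixed in advance, yet they cannot be applied as they stand. Two boundary scores belong to two strata each. The measure changes from a mean to an unqualified score between the medium and high strata. One group of eligible patients has no value on the stratifying variable. Someone must settle these points later, and if that happens after outcomes are known, the sub-analysis is no longer fully pre-defined.

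The undefined mean raises a second issue. If it averages scores taken after randomisation, the stratum depends on something treatment may change, and on the assessments that also determine the primary outcome of delirium- and coma-free days (DCFDs). Patients on haloperidol who land in a given stratum could then have started out sicker than their placebo counterparts, and the within-stratum comparison would no longer be a randomised one.

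Motor subtype raises the same question of timing. The introduction names the response of hyperactive versus hypoactive delirium as something earlier trials did not evaluate.

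**Working it through.** **The plan's own figure.** The sample size section gives "from 3.2 DCFDs in the placebo group to 4.2 in the haloperidol group" and "SD in both groups is equal to 4.2", at 90% power and p<0.05 (sidedness not stated; two-sided reproduces the figure).

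n per arm = 2 × (1.960 + 1.282)² × 4.2² / 1² ≈ 370.8, rounded up to 371, or 742 in total. This agrees with the protocol and is not in dispute. No subgroup size or power is stated.

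**Overlap.** The positive integer scores are 4, 5, 6, 7 and 8. Low covers 4 and 5, medium 5 to 7, high 7 and 8. Scores 5 and 7 each have two strata: 2 of 5. If every combination of scores 4 to 8 were equally likely (an assumption), a mean would fall exactly on 5 or 7 in:

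- 1 assessment: 2/5 = 40%
- 2 assessments: 6/25 = 24%
- 3 assessments: 20/125 = 16%
- 6 assessments: 852/15,625 = 5.5%

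**Instrument.** A patient who qualifies on CAM-ICU and is followed on CAM-ICU has no ICDSC score and so no severity stratum. The other three sub-analyses are not defined by ICDSC and do not have this gap.

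**Possible bias.** The documents give no figure for a drug effect on ICDSC or for the relation of ICDSC to DCFDs, so these values are assumptions. In a simulation of 400,000 patients allocated 1:1:

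- latent severity u has SD 1 ICDSC point;
- the pre-dose score is 5.5 + u + error (SD 0.7), rounded and held to 4-8;
- six study-period scores have the same form, less the drug's reduction on haloperidol, held to 0-8;
- DCFD = 3.7 - 1.5u + true effect + error (SD 3.9). Here 3.7 is the midpoint of 3.2 and 4.2, and the SD is √(1.5² + 3.9²) ≈ 4.2, as in the protocol;
- shared boundary values go to the higher band.

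The table shows haloperidol minus placebo in DCFDs, as the range over the three strata. The last column also spans two ways of averaging: positive scores only, or all scores.

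| ICDSC reduction | True effect (days) | Strata on pre-dose score | Strata on study-period mean |
|---|---|---|---|
| 0 | 0 | -0.03 to +0.04 | -0.02 to +0.07 |
| 0.5 | 0 | -0.04 to +0.02 | -0.63 to -0.45 |
| 1 | 0 | -0.03 to +0.04 | -1.29 to -0.95 |
| 0 | 1 | 0.97 to 1.03 | 0.97 to 1.05 |
| 0.5 | 1 | 0.94 to 1.01 | 0.34 to 0.51 |
| 1 | 1 | 0.93 to 1.02 | -0.26 to +0.01 |

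Pre-dose strata recover the true effect throughout. Study-period strata do so only when the drug leaves ICDSC unchanged. If all study-period scores are averaged, about 7% to 18% of patients have a mean below 4 and fit no stratum.

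**The case against.** A reader might infer that the strata can only be formed after randomisation and that the subgroup effects would therefore be biased. The document does not say so. It states no window for the mean. Qualifying delirium may arise on any ICU day, screening takes place every 8-hour shift, and some patients arrive already delirious, with that duration recorded, so several scores before randomisation can exist. The same applies to a mixed subtype. The lowest band also starts at the eligibility threshold of 4, which speaks against averaging every study-period score. All of this stands.

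There is some evidence the other way. One positive assessment suffices for entry, consented patients can be randomised at any hour once delirium appears, and the scheduled repeated scoring is in the study period. A mean over that period is a plausible reading, but no more than that.

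It is also fair to say that lowering ICDSC with no change in DCFDs is a strained scenario, since delirium is itself defined by ICDSC ≥4. The rows with a true 1-day effect are included for that reason, but every row remains an illustration.

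Finally, the averaging window and the motor-subtype rule are details that may properly wait for the analysis plan. That defence does not reach the overlap, the inconsistent use of the mean or the CAM-ICU gap, because there the printed rule itself fails.

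**Conclusion.** The severity sub-analysis cannot be carried out as printed. Scores 5 and 7 have no unique stratum, the mean is undefined and used in two of three strata, and CAM-ICU-only patients cannot be placed. These are certain from the text.

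The overlap causes ambiguity, not bias. The CAM-ICU gap mainly costs precision and generalisability, and does not bias the arms if the instrument is set before randomisation, for example by site.

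Bias is conditional. It needs study-period scores in the mean and a drug effect on those scores. Under the assumed parameters it then runs from about 0, through about -0.5 day for a 0.5-point reduction, to about -1 day for a 1-point reduction, against a target difference of 1 day. A different slope or error would change these figures.

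For motor subtype the text contains no error, only an unstated rule. The primary analysis and the sample size are not affected.

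**What to change.** Define severity from the ICDSC at the qualifying assessment, or from the last one before the first dose, and say which. Use non-overlapping bands of 4-5, 6 and 7-8, or model a continuous treatment-by-ICDSC interaction on DCFDs. The interaction is attractive because the middle band then holds a single score. State that patients without an ICDSC score are left out of this sub-analysis only, and report how many there are.

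Classify motor subtype only from information available before the first dose, after checking that it is recorded. Table 1 places RASS and CAM-ICU/ICDSC in the study period rather than at enrolment, and neither is in the listed baseline data, so the availability of pre-dose values should be confirmed for both sub-analyses.

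The cost is mainly wording in the analysis plan, before database lock. The small downside is that CAM-ICU-only patients drop out of the severity sub-analysis and fewer patients may be classed as mixed-type.

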**Methods and analysis:**

EuRIDICE is a prospective, multi-centre, randomised, double-blind, placebo-controlled trial. Study population consists of adult intensive care unit (ICU) patients without acute neurological injury who have delirium based on a positive Intensive Care Delirium Screening Checklist (ICDSC) or Confusion Assessment Method for the ICU (CAM-ICU) assessment. Intervention is intravenous haloperidol 2.5 mg (or matching placebo) every 8 hours, titrated daily based on ICDSC or CAM-ICU positivity to a maximum of 5 mg every 8 hours, until delirium resolution or ICU discharge. Main study endpoint is delirium and coma-free days (DCFD) up to 14 days after randomisation. Secondary endpoints include (1) 28-day and 1-year mortality, (2) cognitive and functional performance at 3 and 12 months, (3) patient and family delirium and ICU experience, (4) psychological sequelae during and after ICU stay, (4) safety concerns associated with haloperidol use and (5) cost-effectiveness. Differences in DCFDs between haloperidol and placebo group will be analysed using Poisson regression analysis. Study recruitment started in February 2018 and continues.

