On randomisation, the study drug with the corresponding randomisation kit numbers 1–8 (based on eight medication batches consisting of either haloperidol or placebo) will be obtained from the hospital pharmacy of each participating ICU. Each box from a batch/kit contains 10 ampules (5 mg/1 mL) of haloperidol or placebo. If all ampules are used, a new box from the same medication kit number with 10 ampules will be used. Study drugs are administered on prescription in the electronic patient data management system (PDMS) and are double-checked by ICU nurses before administration, which is similar to regular practice. Furthermore, the kit number was noted on randomisation in the medical file and the kit number could be retrieved at any time from the PDMS after first prescription on randomisation.

Blinding of the medication will be performed by the pharmacy, based on a randomisation list that will be generated electronically through a randomisation module in the EDC system of ALEA. Randomisation will be stratified per study centre (ie, equal number of patients in both study groups; see ‘Statistical analysis’ section). Only the involved pharmacists and the trial statistician are aware of the contents of each medication kit. Only the local (site) pharmacists are able to unblind study treatment of a patient in case of an emergency. Except for the hospital’s pharmacist responsible for the randomisation list, all other involved personnel with the study, caregivers, patients or their representatives will remain unaware of the treatment groups until the time of Database Lock. The unblinding procedure is specified in online supplemental appendix 7.

10.1136/bmjopen-2019-036735.supp7Supplementary data

Follow-up procedures will be performed according to designated SOPs. When possible and preferred by patients or families, questionnaires will be sent or visits planned at home when possible, for example, for incapacitated participants.

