### Withdrawal of individual subjects

Subjects can leave the study at any time for any reason if they wish to do so without any consequences. The investigator can decide to withdraw a subject from the study for urgent medical reasons.

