### Follow-up of subjects withdrawn from treatment

Data of withdrawn patients will remain in the database for statistical analysis purposes but will not be subject to follow-up. When patients specifically withdraw their consent for usage of their data, these data will be removed from the database and excluded from all analyses.

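### Follow-up ends for withdrawn patients, yet 28-day and 1-year mortality is to be a binary outcome in all randomised patients; vital status should still be collected after withdrawal

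*Protocol article*

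**What the plan says.** The abstract of the protocol article gives the time points: "Secondary endpoints include (1) 28-day and 1-year mortality". The lists of secondary outcomes repeat them at 28 days and 12 months after randomisation.

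The Statistical analysis section (Primary and secondary study parameter(s)) adopts intention to treat and states "All randomised participants will be included". On mortality it says only "Mortality risk will be assessed as a binary endpoint". It leaves further detail to a separate analysis plan, to be drawn up before database lock.

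Under Withdrawal of individual subjects, patients may leave at any time, and "The investigator can decide to withdraw a subject from the study for urgent medical reasons". The next section is headed "Follow-up of subjects withdrawn from treatment" and states "Data of withdrawn patients will remain in the database for statistical analysis purposes but will not be subject to follow-up". It then adds: "When patients specifically withdraw their consent for usage of their data, these data will be removed from the database and excluded from all analyses".

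The article does not mention obtaining vital status after withdrawal from records or a registry.

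**The concern.** A binary mortality outcome at a fixed day needs to be known, dead or alive, for every patient on that day. A patient withdrawn on day 10 and not followed contributes ten days known alive and no status at day 28 or 1 year. The rule on withdrawn patients therefore creates gaps that the promise to include all randomised patients does not allow for. Withdrawals before day 28 affect both mortality outcomes; withdrawals between day 28 and 1 year affect only the second.

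The two simplest ways to close the gap are not neutral. Only a living patient can be withdrawn, so leaving these patients out removes people who had already survived part of the period. Counting them as alive ignores every later death among them. If withdrawal differs by arm, either handling can create a mortality difference that is not there, or hide one that is.

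This differs from a detail that an analysis plan can settle later. The no-follow-up rule governs data collection, and a plan finished just before database lock cannot restore vital status that nobody recorded.

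**Working it through.** **The plan's own figure.** The only calculated design figure is 371 per arm, for the primary outcome: 2 × (1.96 + 1.2816)² × 4.2² / 1² = 370.7, rounded up to 371. It reproduces with two-sided 5% and 90% power. It says nothing about mortality; it is used below only as the number per arm.

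**Inputs.** From the document: 371 per arm, and 575 expected ICU survivors of 742, so 167 ICU deaths, or 22.5%. Not in the document, so assumed: true 1-year mortality of 35% in both arms, 15% dead by day 14, and a share w withdrawn at day 14 (2% in one arm, 8% in the other; about 7 and 30 patients) with the same later risk as the other patients alive at day 14.

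**Formulas**
- Risk after day 14 among those alive then: 1 − 0.65/0.85 = 0.235.
- Left out: (0.15 + (0.85 − w) × 0.235) / (1 − w).
- Counted alive: 0.15 + (0.85 − w) × 0.235.
- Counted dead: the previous line plus w.
- Kaplan-Meier: 1 − 0.85 × (0.65/0.85) = 0.35, whatever w is.

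| Handling of withdrawn patients | 2% arm | 8% arm | False difference (8% arm minus 2% arm) |
|---|---|---|---|
| Kaplan-Meier, censored at withdrawal | 35.0% | 35.0% | 0 |
| Left out | 35.2% | 36.0% | +0.8 points |
| Counted alive | 34.5% | 33.1% | −1.4 points |
| Counted dead | 36.5% | 41.1% | +4.6 points |

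The standard error of the difference is √(2 × 0.35 × 0.65 / 371) = 0.035, or 3.5 points. Leaving out gives 0.8/3.5 = 0.2 standard errors, and counting as alive gives 1.4/3.5 = 0.4. Best- and worst-case bounds on the difference run from 33.1 − 36.5 = −3.4 to 41.1 − 34.5 = +6.6 points. With no withdrawals every line gives 35.0%.

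**Range.** Now let the true risk p be 22.5% to 45%, equal in both arms, with withdrawal of 5% v 10%, and let withdrawn patients have rr times the risk of retained patients (rr = 1 or 1.5). The retained risk is r0 = p / (1 − w + w × rr). Leaving out gives r0; counting as alive gives r0 × (1 − w).
- Smallest case, p = 22.5%, rr = 1: counted alive 21.4% v 20.3%, a false difference of 1.1 points; left out, none.
- Largest case, p = 45%, rr = 1.5: counted alive 41.7% v 38.6%, 3.1 points; left out 43.9% v 42.9%, about 1 point.

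Leaving out is unbiased in this range only at rr = 1. In the day-14 example a leaver's 1-year risk is 0.235 against 0.352 in the 2% arm's retained patients, so rr is about 0.67 although leaving carries no prognostic information. Having survived to day 14 is enough to cause the bias.

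**The case against.** **Is the binary endpoint itself wrong?** A reader might infer that it forces the analyst either to drop withdrawn patients or to count them as survivors. The document does not say so. It names no estimator and no rule for missing status. Multiple imputation, weighting, bounds, or a Kaplan-Meier risk at the fixed day would all be compatible with it, and the choice is commonly left to the analysis plan. With complete vital status a binary endpoint is valid. This objection stands, and it places the fault in the no-follow-up rule, not in the mortality sentence.

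**Is Kaplan-Meier better?** Only if withdrawal is unrelated to prognosis, which is doubtful when the investigator may withdraw patients for urgent medical reasons. Take the same example but double the leavers' later risk to 0.47 (an assumption). True risk in the 8% arm is 0.15 + 0.77 × 0.235 + 0.08 × 0.47 = 36.9%, against 35.0% by Kaplan-Meier and 36.0% when leavers are left out. In the 2% arm the figures are 35.5%, 35.0% and 35.2%. Here leaving them out is closer to the truth in both arms. This also stands: no analysis replaces the missing status, so collecting it comes first and bounds are needed for the rest.

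**Does everyone who stops study drug lose follow-up?** The section heading invites that reading, because it speaks of treatment. The text does not establish it: the sentence concerns withdrawn patients, and the preceding section is about leaving the study. The scope is unclear and needs stating.

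**Is a centre term missing?** A reader might add that the mortality sentence has no centre term although "Randomisation will be stratified per study centre". Silence on the model for a secondary outcome in a condensed article is not an error, so this is no part of the point.

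**Is it large?** A fourfold imbalance in withdrawal is a strong assumption in a double-blind trial, and it still moves the result by less than half a standard error.

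**Conclusion.** The conflict is real and minor. The article ends follow-up for withdrawn patients and also promises a mortality status for every randomised patient at 28 days and 1 year. For anyone withdrawn alive before the time point, both cannot be met.

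Its size cannot be read from the document, which gives neither a withdrawal rate nor a 28-day or 1-year mortality. The illustrative false difference of 0.8 to 1.4 points rests on the assumed imbalance of 2% v 8%, on withdrawal at day 14, and on equal later risk. It disappears if nobody is lost, and also if losses and risks are equal in both arms. The documents do not support the conclusion that the mortality results will be materially wrong, or that a binary outcome is unsuitable.

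**What to change.** 1. Amend the section on withdrawn patients. Vital status and the date of death or last contact continue to be collected to 1 year after withdrawal from treatment or from study procedures, unless the patient refuses this. State which kinds of withdrawal the section covers.
2. In the Statistical analysis section, estimate the 28-day and 1-year mortality risks and their difference by Kaplan-Meier, with any remaining unknown status censored at the last date known alive. With complete follow-up this equals the binary risk, so the quantity estimated does not change.
3. Add best- and worst-case bounds as a sensitivity analysis, because censoring assumes that withdrawal is unrelated to prognosis.
4. Report by arm how many patients have unknown status at each time point, and how many were removed because they withdrew consent to use of their data. The first change cannot reach that last group.

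The cost is protocol and analysis-plan wording, matching consent wording where needed, and one date per patient. No new patients or visits are required. Recruitment has already started, so patients withdrawn earlier can be covered only as far as their consent allows.
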